### Assignment of interventions

#### Randomization, sequence generation, and allocation concealment

Upon participant enrollment, patients will be randomized to one of two arms, with a 1:1 allocation. The randomization sequence will be computer-generated by a member of the research team. An independent research coordinator will handle the treatment allocation process. This coordinator will ensure allocation concealment by using sequentially numbered, sealed opaque envelopes. The allocation sequence will be provided to an attending staff pain medicine physician.

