### Trial design

The EndParl study is designed as a prospective, multicentre, active comparator-controlled, non-inferiority randomized trial with two parallel groups and blinding of participants and outcome assessors. Randomization will occur on the day of the procedure and will be done to one of two arms on a 1:1 allocation basis. The randomization sequence will be computer-generated, and allocation concealment will be ensured by sequentially numbered, sealed opaque envelopes. This process will be carried out by an independent research coordinator, who will not be involved in the recruitment process or conduct of the trial. An unblinded physician will do the procedure but they will not be involved in assessing the outcomes. A blinded member of the research team will perform follow-up outcome assessments. Treating physicians, participants, close contacts, trial coordinators, and primary outcome analysts will be blinded to treatment allocation.

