### Participant timeline

Participants who meet the inclusion criteria will be reached by research coordinator for possible enrollment. Participants will be enrolled in the study after consenting and before receiving a RFN of the CMBN. The goal of this trial is to demonstrate non-inferiority of the end-on technique as compared to the conventional parallel technique for RFN of the CMBN. The baseline study questionnaires will be completed within 4 weeks before the study intervention. Baseline data on sleep and physical activity will also be collected using actigraphy over 1 week prior to the trial intervention and for at least 1 week prior to the follow-up at 1 month after the intervention. Routine scheduled study follow-ups will occur at 1, 3, 6, and 12 months after the study interventions, at which times all follow-up measures will be obtained (Table 2, Fig. 1). The follow-up at 1 and 3 months will be in-person whereas the follow-ups at 6 and 12 months may be virtual (video/phone) to assess trial-relevant outcomes.

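### The protocol gives two different times of randomisation, and one sentence, read literally, releases the allocation sequence to a clinician

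*Protocol article*

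**What the plan says.** Two sections of the protocol article describe randomisation.

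- **Trial design:** "Randomization will occur on the day of the procedure and will be done to one of two arms on a 1:1 allocation basis". The sequence is computer-generated and concealed in numbered, sealed envelopes. The process is run by an "independent research coordinator, who will not be involved in the recruitment process or conduct of the trial".
- **Randomization, sequence generation, and allocation concealment:** "Upon participant enrollment, patients will be randomized to one of two arms, with a 1:1 allocation". The sequence is "computer-generated by a member of the research team". An independent coordinator handles allocation with the envelopes, and then: "The allocation sequence will be provided to an attending staff pain medicine physician".

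Four other sections bear on this.

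- **Participant timeline** places enrolment after consent and before the neurotomy. It adds: "The baseline study questionnaires will be completed within 4 weeks before the study intervention". Baseline actigraphy covers the week before the intervention.
- **Research ethics approval** requires written consent before any study activity.
- **Blinding mechanism** says that the staff physician who performs the procedure is given the assignment, and that this physician takes no part in assessing outcomes.
- **Post-procedural management** provides for people who are randomised but not treated: they are not reassigned, and their data are still collected.

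**The concern.** There are two problems, both in what the text states.

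First, the time of randomisation differs between the sections, and a site cannot tell which to follow. The choice decides whether baseline data are collected before or after allocation. It also decides how long a gap lies between allocation and treatment, during which a participant can withdraw or be cancelled.

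Second, the section that governs concealment sets up sealed envelopes under an independent coordinator and then says that the sequence goes to a treating physician. Someone who holds the sequence knows the coming assignments. If that person also has a say in who enters the trial or when they are booked, patients can be selected or deferred according to the next allocation. Blinded follow-up cannot repair a bias that arises before allocation.

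**Working it through.** No figure in the plan depends on this point, so the check is a comparison of the texts.

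**Timing**

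1. Consent comes before every study activity (Research ethics approval).
2. Wearing the actigraphy device for a week before the procedure is a study activity (Participant timeline). Consent therefore falls at least 1 week before the procedure.
3. Enrolment follows consent and precedes the neurotomy (Participant timeline). No section ties it to the procedure day.
4. Randomising at enrolment: if enrolment follows consent promptly, allocation falls at least 1 week before the procedure and before the actigraphy baseline. It may also fall before questionnaires completed in the 4-week window.
5. Randomising on the procedure day: the actigraphy week has ended, and the questionnaires can be complete, before allocation.

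| Baseline item | Allocation at enrolment | Allocation on the procedure day |
|---|---|---|
| Actigraphy week | after allocation, if enrolment follows consent promptly | before allocation |
| Sleep and quality-of-life questionnaires | possibly after allocation | can be before allocation |
| Pain score (NRS) and Neck Disability Index | qualifying values should exist already, as both are entry criteria in Table 1 | the same |
| Gap in which an allocated person can go untreated | at least 1 week, if enrolment follows consent promptly | hours |

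**Who is given what**

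1. In the randomisation section, *sequence* first means the computer-generated list. Later in the same short paragraph the same word names what the physician is given.
2. In the Blinding mechanism section the operator is given the *assignment*, that is, one participant's arm.
3. The operator is barred from outcome assessment (Trial design; Blinding mechanism). No section bars the operator from recruiting, judging eligibility or scheduling, and none assigns the operator these tasks.
4. Participants are recruited from the clinics where the trial is conducted (Trial setting; Feasibility of recruitment). Some influence of the operator on entry or booking is therefore possible, though it is not stated.

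**Who generates the sequence**

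The Trial design section can be read as giving generation and concealment to the independent coordinator, or concealment alone. The randomisation section gives generation to a research team member and does not say whether that person recruits or treats. This is an ambiguity, not a plain contradiction.

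**The case against.** The strongest reply is that the wording is loose and the design sound. An unblinded operator must learn the current participant's arm. The Blinding mechanism section says just that, and the sentence before the disputed one describes proper envelopes. On this view *sequence* is a slip for *assignment*. Eligible patients are approached by a research coordinator, and entry depends on two positive diagnostic blocks and score thresholds, so the operator's room for selection is limited. This reply has force. A reader might infer that concealment is defeated as planned, and the document does not show that. Concealment fails only if the list itself is released and its holder can influence entry or timing. The text neither says nor excludes either condition.

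Three further inferences are tempting and are not supported.

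- *The responder outcome is compromised because baseline NRS follows allocation.* NRS at baseline evaluation is an inclusion criterion, so a value should exist before enrolment under either timing. Participants and assessors are also to be blinded.
- *Untreated participants will dilute the difference enough to favour non-inferiority.* The protocol gives no rate of loss before the procedure; its 10% is an overall dropout rate. The Statistical methods section also plans a per-protocol analysis alongside intention to treat, which is the usual check on such dilution. No figure can be put on this.
- *The sections name two different sequence generators.* A coordinator may also belong to the research team, so the texts can be reconciled.

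It can also be said that enrolment might be completed formally on the procedure day, which would remove the timing conflict. No section says so, and the Participant timeline does not suggest it. The conflict on timing therefore stands. So does the mismatch between *sequence* and *assignment*. That the article is condensed answers neither, since both are conflicting statements and not omissions.

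**Conclusion.** The point holds as an inconsistency that should be corrected. The two randomisation times conflict. Under the enrolment reading, and assuming that enrolment follows consent promptly, allocation precedes the actigraphy baseline, may precede some questionnaires, and leaves at least a week in which allocated participants can be lost before treatment. Actigraphy supplies secondary outcomes only, which limits the direct effect on the primary results.

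The sentence on the sequence, if followed as written, would undermine the envelopes, because it would disclose future assignments to a clinician who is not excluded from recruitment, eligibility or scheduling. Whether sites would follow it literally is unknown. The size of any selection bias cannot be derived from the document. The case for acting rests on the fact that such a bias could not be repaired afterwards, while the correction costs very little.

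**What to change.** In the randomisation section of the protocol:

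1. Replace randomisation at enrolment with randomisation on the procedure day, after all baseline questionnaires and the actigraphy week have been recorded. This matches the Trial design section.
2. State that the independent coordinator opens the next numbered envelope and tells the operator that participant's assignment only.
3. Delete the sentence that provides the allocation sequence to the attending physician.
4. State that whoever generates the sequence has no recruiting or treating role.

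The cost is a protocol wording change and an instruction to the sites. The coordinator and the envelopes are already planned, and the sample size and analysis are not affected. Recruitment began in March 2023, so the trial team should also record which timing and which hand-over were used for participants already randomised.

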### Blinding

#### Blinding mechanism

Participants, physicians, and all outcome assessors will all be blinded during the conduct of the trial and statistical analysis. Assessors will remain blinded to their group assignments throughout the study. A Staff Pain Medicine physician with at least 5 years of experience in performing RFN of the CMBN and who is not involved in the assessment of outcomes will receive the randomization assignment and perform the procedure using the assigned technique. Biostatisticians who will analyze the data will be blinded to group allocation and the two study groups will be represented as I and II on the study database with no other identifiers.

#### Emergency unblinding

Emergency unblinding will only occur when knowledge of the treatment assignment is necessary for the immediate medical management of a participant. This can occur in the occurrence of serious adverse events, or by decision of the Principal Investigator or the Data Safety Monitoring Board. Time and reason for emergency unblinding will be recorded. In the event of emergency unblinding, the timing, reason, and personnel involved will be recorded in the CRF, and blinding will be maintained in as many other trial personnel as possible.

### Data collection

#### Data collection methods

Data will be gathered using data collection forms, and the research coordinator will input the information into a password-protected electronic database (Microsoft Excel platform). Our data collectors are experienced research assistants who have been trained in Good Clinical Practice (GCP). There will be regular meetings between the data collectors and the trial Principal Investigator. We will use validated questionnaires for assessing pain and related domains. Patients will be followed closely at dedicated time points to promote retention and collection of follow-up data.

#### Baseline data

Baseline data will include participants demographics, pain intensity as measured by NRS score, physical activity, sleep duration both measured by Actigraphy, sleep quality measured by PSQI, physical function as measured by the NDI, opioid and non-opioid analgesic intake.

#### Intervention data

Duration of the procedure will be recorded as well as cost, discomfort, dose of radiation, and any intra- and immediate post-procedural complications.

#### Follow-up data

The following data will be collected at 1, 3, 6, and 12 months following the interventions. The data points will include pain intensity as measured by NRS score, participant impression of improvement as measured by PGIC, opioid and non-opioid analgesic intake, physical activity as measured by the NDI, health-related quality of life measured by EQ-5D-5L, physical activity and sleep both measured by Actigraphy, and adverse effects.

#### Data management and confidentiality

All trial data will be checked on a regular basis for errors and missing data. Trial data from the actigraphy device will be exported as a comma-separated values (CSV) file for analysis. It will be locally synced on an institutional research laptop. Participants’ contact information and identifying information will be encrypted and stored in a separate database. Identifying information will be deleted once follow-up is completed. The Institutional Research Ethics Board (IREB) audits trial records and collected personal health information to verify that the information collected for the trial is correct and to make sure the trial is following institutional regulations. Completed questionnaires collected during the trial visits will be labeled with a unique trial code. No patient names will be used. The information that links the unique trial code to the participant will be kept in a secure area in our institute, and it will be distinct from the participants’ trial data. This information can only be accessed by research team members who are involved in the trial. All records and documents pertaining to the trial will be retained by the trial sites for 5 years from the completion of the trial.

In the event of personal health information disclosure to an unauthorized party, the following will be done: any further release of information will be stopped, as much information as possible will be retrieved, IREB privacy Offices will be contacted, and further actions would be taken based on their recommendations.

### Statistical methods

A statistician will be consulted to assist in data analysis and interpretation. Descriptive information for the sample’s study measures will include frequency distributions or proportions for categorical variables and means (standard deviations) or medians (interquartile ranges) (if non-normally distributed) for the continuous variables. To compare data between the two groups, categorical outcomes will be analyzed with the chi-square test and continuous variables will be analyzed with independent *t*-tests (or Wilcoxon rank sum test, as appropriate). A two-sided *p*-value of < 0.05 will be considered statistically significant. Both intention-to-treat (based on study arm allocation) and per-protocol (based on the participants who adhered to the study protocol and provided data at study outcome time points) analysis will be performed and reported.

Correlation between reduction in pain and improvement in function will be evaluated with a longitudinal model of changes from baseline to 3-month, 6-month, and 12-month follow-ups. An intention-to-treat strategy will be used for all analyses. Differences in treatment effects and 95% confidence intervals for pain and secondary outcome scores will be calculated using chi-square and odds ratios for dichotomous variables, and ANOVA (with *t*-tests for pairwise comparisons) and Mann–Whitney for continuous variables, as indicated. A set of logistic regression models for categorical outcome at 3 months will be created using variables hypothesized to have an effect on treatment (gender, intensity of pain, nature of injury), as well as those found to have a *p*-value less than 0.20 in univariate analysis. A secondary analyses based on data from participants who undergo unilateral versus bilateral RFN with each of the two study treatments is also planned. Missing data will be imputed using the “last observation carried forward” approach if at least 80% of the outcome data is available for the participant. All analyses will be performed using the SPSS program.

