### Hypotheses

The primary hypotheses for this non-inferiority trial are that end-on lesioning for RFN of the CMBN is non-inferior to the parallel conventional technique for its impact on the intensity of pain relief and the proportion of patients with a positive analgesic response at 3 months after the intervention in patients with chronic, moderate-to-severe neck pain in the context of cervical zygapophyseal joint syndrome. The secondary hypotheses are that end-on lesioning for RFN of the CMBN is non-inferior to the parallel conventional technique for its impact function, quality of life, sleep, adverse effects of the interventions, analgesic intake at specified time points within 1 to 12 months after the interventions in patients with chronic, moderate-to-severe neck pain in the context of cervical zygapophyseal joint syndrome.

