### Outcomes

Patients will be assessed at baseline and 1, 3, 6, and 12 months after the study interventions. The assessment schedule and parameters are summarized in Table 2.

**Table 2 Tab2:** EndPaRL assessment schedule

**Outcome**	**Measure**	**Baseline**	**Immediate after procedure**	**1 month after procedure**	**3 months after procedure**	**6 months after procedure**	**12 months after procedure**
**Patient demographics**		**X**					
**Pain intensity**	NRS	**X**	**X**	**X**	**X**	**X**	**X**
**Neck disability**	NDI	**X**	**X**	**X**	**X**	**X**	**X**
**Global improvement**	PGIC			**X**	**X**	**X**	**X**
**Sleep quality**	PSQI	**X**		**X**	**X**	**X**	**X**
**Sleep duration**	In hours and minutes from actigraphy device	**X**		**X**			
**Physical functioning**	Time spent at different activity levels from actigraphy device^b^	**X**		**X**			
**Opioid intake**	Daily OME in mg	**X**		**X**	**X**	**X**	**X**
**Analgesics**	Name and dose	**X**		**X**	**X**	**X**	**X**
**Procedure** **(1) Duration** **(2) Cost** **(3) Discomfort** **(4) Radiation**	(1) In minute (2) In CAD (3) 0–10 (4) Dose in mSv		**X** **X** **X** **X**				
**Complications**	e.g., bleeding, hematoma		**X**				
**Adverse effects**				**X**	**X**	**X**	**X**
**Health-related quality of life**	EQ-5D-5L^a^	**X**		**X**	**X**	**X**	**X**

*CAD* Canadian dollars, *NRS* Numerical Rating Scale, *OME* Oral morphine equivalents

^a^EuroQol 5-level EQ-5D version (EQ-5D-5L); Neck Disability Index (NDI); Numerical Rating Scale (NRS); Patients’ Global Impression of Change (PGIC); Pittsburgh Sleep Quality Index (PSQI)

^b^Data on physical activity and sleep collected using participant-worn actigraphy devices (light/moderate/severe)

The following are the *primary outcomes*:The between-group difference in mean NRS for pain intensity scores at 3 months after the interventions.The between-group difference in the proportion of patients with a positive analgesic response (defined as 50% or greater reduction in the NRS score for neck pain as compared to baseline) at 3 months after the interventions.

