### Sample size

The sample size was calculated using the Statistical Package for the Social Sciences (SPSS, IBM SPSS Statistics) software. A sample size of 72 participants (36 in each treatment group) will provide 80% power to detect a difference (inferiority margin), at 3 months after the intervention, in the mean NRS pain intensity scores (0–10 scale) between the two treatment groups being less than or equal to 1 point, given a standard deviation (SD) of 1.7 at the 0.05 significance level (alpha) using a two-sided two independent sample *t*-test. To satisfy both the non-inferiority and superiority hypothesis, we plan to recruit a total of 80 participants to account for a presumed 10% dropout rate. The sample size calculations and the assumptions underlying it are based on data published on RFN of nerves supplying other axial joints (lumbar facets, sacroiliac) for the relief of spinal pain [12, 13]. The chosen non-inferiority margin of less than or equal to 1 point (10%) is reasonable because a minimal clinically important difference in pain scores for a treatment to be considered efficacious is 2 points or 30% [14]. A non-inferiority study is justified to compare the end-on and parallel RFN lesions because similar efficacy is expected but there may be a lower incidence of adverse effects (e.g., patient discomfort) and better resource utilization (e.g., faster procedure time, lower radiation dose) with the end-on RFN technique.

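### The hypotheses are non-inferiority, but the analysis section tests only for a difference and never links its planned confidence intervals to the 1-point margin

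*Protocol article*

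**What the plan says.** Protocol article, Hypotheses: "The primary hypotheses for this non-inferiority trial are that end-on lesioning for RFN of the CMBN is non-inferior to the parallel conventional technique", both for pain intensity and for the proportion with a positive analgesic response at 3 months.

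Protocol article, Sample size: "The chosen non-inferiority margin of less than or equal to 1 point (10%) is reasonable". The calculation uses 36 per arm, "given a standard deviation (SD) of 1.7", 80% power and a two-sided 0.05 t-test. The paragraph mentions both a non-inferiority and a superiority hypothesis.

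Protocol article, Outcomes: the second primary outcome is "The between-group difference in the proportion of patients with a positive analgesic response" at 3 months. No margin is given for it here or elsewhere.

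Protocol article, Statistical methods: "categorical outcomes will be analyzed with the chi-square test and continuous variables will be analyzed with independent" t-tests, or Wilcoxon where appropriate. Two-sided p < 0.05 is the only stated threshold. The section also plans:
- 95% confidence intervals for pain and secondary scores;
- odds ratios for dichotomous outcomes, and ANOVA or Mann–Whitney for continuous ones;
- two analysis sets ("Both intention-to-treat (based on study arm allocation) and per-protocol"), followed in the next paragraph by "An intention-to-treat strategy will be used for all analyses".

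Neither the margin nor non-inferiority is mentioned in that section. The Additional studies section makes a later cost-effectiveness study depend on non-inferiority being achieved, without saying what result would achieve it.

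**The concern.** A t-test or chi-square test at p < 0.05 has a null hypothesis of no difference. The trial's null hypothesis is that end-on is worse by at least the margin. A result can fail to reach p < 0.05 and still be compatible with a deficit larger than 1 point. The one threshold the analysis section gives therefore does not answer the primary question, and the margin plays no part in the stated analysis.

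Three features add to this:
- The permitted switch to a rank test gives a p-value that cannot be set against a margin on the mean.
- For responders there is no margin at all, so even a well-constructed interval could not be judged.
- The two statements about analysis sets do not agree on their face.

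At stake is the main claim of the trial. If the rule is chosen after the results are seen, a non-inferiority conclusion loses most of its weight.

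**Working it through.** **Inputs.** Margin 1 point, SD 1.7, 36 per arm, 80% power, two-sided alpha 0.05 and 10% dropout come from Sample size. The true difference is not given as a number. I take it as 0, because that section expects similar efficacy. D denotes mean 3-month NRS, end-on minus parallel, so a positive D means end-on is worse.

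**Step 1: reproduce the 72.** Per arm, n = 2 × SD² × (z_alpha + z_beta)² / margin², with 2 × 1.7² = 5.78.
- One-sided 0.05: 5.78 × (1.645 + 0.842)² = 35.7, so 36 per arm and 72 in total. This matches the plan. With dropout, 72 / 0.9 = 80, which also matches.
- Two-sided 0.05, equivalent to one-sided 0.025: 5.78 × (1.960 + 0.842)² = 45.4, so 46 per arm and 92 in total. With dropout, 92 / 0.9 = 102.2, so 103.

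The 72 therefore corresponds to a one-sided 0.05 test (a 90% interval), not to the two-sided 0.05 that the section names.

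**Step 2: precision at 36 per arm.** SE = 1.7 × √(2/36) = 0.401, with 70 degrees of freedom.
- 95% half-width: 0.80. The upper limit is below 1 only if the observed D is below 1 − 0.80 = 0.20.
- 90% half-width: 0.67. The observed D must be below 1 − 0.67 = 0.33.

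**Step 3: where the two criteria part.** An observed deficit between about 0.20 and 0.80 is non-significant, yet its 95% upper limit exceeds 1. For example, D = 0.5 gives t = 0.5 / 0.401 = 1.25, p = 0.22 and a 95% interval from −0.30 to 1.30.

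**Step 4: behaviour of each rule** (400,000 simulated trials per row, 36 per arm, SD 1.7):

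| True D | p ≥ 0.05 | 95% upper limit < 1 | 90% upper limit < 1 |
|---|---|---|---|
| 0 | 95% | 69% | 80% |
| 0.5 | 77% | 23% | 34% |
| 1.0 | 31% | 2.5% | 5% |

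The 31% agrees with the exact calculation: the t-test has power 0.692 against a 1-point difference, and 1 − 0.692 = 0.308.

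**Step 5: power of an interval rule at true D = 0.** With 72 evaluable, exact t power is 69% for the 95% interval and 80% for the 90% interval. If all 80 recruited were evaluable (40 per arm), the 95% rule would have 74%.

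**The case against.** The strongest reply is that the ingredients are all present. The analysis section plans 95% intervals for pain, the Sample size section gives a margin, and both intention-to-treat and per-protocol analyses are promised. Only the sentence joining them is absent, and a published article may leave that to an analysis plan that is not shown. Tests of no difference also have a proper use here: for the superiority hypothesis and for procedural outcomes such as duration, radiation and discomfort. The sentence on intention-to-treat for all analyses follows directly on the longitudinal-model sentence and may refer only to that.

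Much of this stands. A reader might infer that the trial cannot establish non-inferiority. The documents do not support that: the interval needed for pain will be calculated, and a significant result favouring end-on would itself imply non-inferiority. A reader might also infer that the investigators will treat a non-significant p as non-inferiority. No section says so; the article says only that p < 0.05 counts as statistically significant. The 31% describes that misreading, not a rule in the protocol. Odds ratios do not prevent a risk difference from being reported, and which analysis set governs the claim is commonly left to an analysis plan.

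The reply does not remove the main point. The article is not silent on the criterion. It states one, and that one addresses a different hypothesis from the one declared. An analysis plan that applied the margin would have to add to or override the published text. The missing responder margin also cannot be recovered from anything in the article.

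**Conclusion.** The point holds in this form: the stated analysis does not test the stated primary hypotheses, because its intervals and its margin are never joined, and the second primary outcome has no margin. It concerns the analysis as written, not what the data could show.

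If non-significance were taken as non-inferiority, the false-pass rate at a true 1-point deficit would be about 31%, against 2.5% or 5% under an interval rule. This assumes 36 evaluable per arm, SD 1.7 and roughly normal means. The power figures also assume no true difference, which the article implies but does not quantify.

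The repair exposes a second matter. The 80% power claimed for 72 participants holds for a 90% interval, not for the 95% interval that the analysis section names. This needs correcting before unblinding.

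**What to change.** Amend Statistical methods, before unblinding, as follows:

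- **Decision rule.** Conclude non-inferiority on pain only if the upper confidence limit of the mean 3-month NRS difference, end-on minus parallel, is below 1.0. Report both intention-to-treat and per-protocol results and require them to be consistent. Test superiority only after non-inferiority is shown.
- **Rank tests.** Keep Wilcoxon and Mann–Whitney as sensitivity analyses only.
- **Analysis sets.** Reconcile the sentence that applies intention-to-treat to all analyses with the planned per-protocol analysis.
- **Confidence level.** State it and restate power to match: about 69% with the 95% interval, or about 80% with a 90% interval (72 evaluable, no true difference).
- **Responders.** Report the risk difference with its confidence interval, and either pre-specify a margin or drop the non-inferiority claim for this outcome.
- **Secondary outcomes.** Where no margin exists, report estimates with intervals and make no non-inferiority claim.

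The decision rule costs wording only. The confidence level may cost more. Keeping 95% means accepting about 69% power, or moving to 92 evaluable (103 recruited at 10% dropout, against 80 planned) to reach 80% by the plan's type of calculation. Choosing 90% keeps the planned size but must be declared as a one-sided 0.05 test. Requiring consistency across both analysis sets cannot raise power.

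### The primary 3-month mean NRS comparison is fixed as unadjusted although baseline NRS is collected for everyone; a prespecified baseline-adjusted analysis would gain precision at the cost of one degree of freedom

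*Protocol article*

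**What the plan says.** The first primary outcome, in the Outcomes section of the protocol article, is "The between-group difference in mean NRS for pain intensity scores at 3 months after the interventions". The second is the proportion of responders, "defined as 50% or greater reduction in the NRS score for neck pain as compared to baseline".

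Statistical methods sets the tests. For the first outcome, "continuous variables will be analyzed with independent" t-tests, or a Wilcoxon rank sum test where appropriate. For the second, "categorical outcomes will be analyzed with the chi-square test". Treatment differences and intervals for continuous measures come from "ANOVA (with *t*-tests for pairwise comparisons) and Mann–Whitney for continuous variables, as indicated". No covariate is attached to any of these. The Sample size section also rests on a two-sample t-test.

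Baseline data lists "pain intensity as measured by NRS score", Table 2 marks NRS at baseline, and Table 1 requires a baseline 7-day average NRS of at least 5.

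Covariates enter a model of outcome in one place only: "A set of logistic regression models for categorical outcome at 3 months will be created". These models use three named variables (gender, intensity of pain, nature of injury) plus any with a p-value "less than 0.20 in univariate analysis". The longitudinal model mentioned in the same section relates pain reduction to functional improvement; it is not the between-arm comparison.

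**The concern.** Non-inferiority on mean NRS depends on whether the confidence interval for the difference excludes 1 point, so anything that widens the interval lowers the chance of a conclusive result. If baseline pain predicts 3-month pain, an unadjusted comparison leaves that predictable variation in the error term. The covariate is already measured, so the lost precision buys nothing.

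The screening rule is a smaller matter. Choosing covariates by their univariate p-values in about 72 people makes the adjusted estimate depend on chance selections, and the usual intervals take no account of that selection.

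**Working it through.** **Inputs from the Sample size section:** 36 per arm, SD 1.7, margin 1 NRS point, 80% power, alpha 0.05 described as two-sided. A true difference of 0 is the usual non-inferiority planning assumption.

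**Input not in the article:** the correlation r between baseline and 3-month NRS. It is assumed and shown over a range. The entry cut at NRS 5 or more restricts the baseline range and may keep r low.

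**Step 1: reproduce the stated size.** By the normal approximation, n per arm = 2 × 1.7² × (z for alpha + z for power)² / 1² = 5.78 × (z for alpha + 0.842)².

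- One-sided 0.05: 5.78 × (1.645 + 0.842)² = 35.7, so 36 per arm, or 72 in total. This reproduces the stated figure.
- Two-sided 0.05: 5.78 × (1.960 + 0.842)² = 45.4, so 46 per arm, or 92 in total. This does not.
- Dropout: 72 / 0.9 = 80, as stated.

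Since the stated 72 and the stated two-sided alpha do not agree, both readings are carried below.

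**Step 2: effect of adjustment.** ANCOVA on baseline NRS gives residual SD = 1.7 × √(1 − r²) and SE = residual SD × √(2/36), with 69 degrees of freedom instead of 70. Power is from the noncentral t with noncentrality 1/SE. The half-width is 1.96 × SE.

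| r (assumed) | Variance factor 1 − r² | SE | 95% CI half-width | Power, two-sided 0.05 | Power, one-sided 0.05 |
|---|---|---|---|---|---|
| unadjusted | 1 | 0.401 | 0.785 | 69.2% | 79.6% |
| 0.2 | 0.96 | 0.393 | 0.769 | 70.9% | 81.0% |
| 0.3 | 0.91 | 0.382 | 0.749 | 73.2% | 82.8% |
| 0.4 | 0.84 | 0.367 | 0.720 | 76.6% | 85.3% |
| 0.5 | 0.75 | 0.347 | 0.680 | 81.1% | 88.7% |

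In patient terms, 36 per arm with adjustment is worth 36/0.96 = 37.5 at r = 0.2, 36/0.91 = 39.6 at r = 0.3, and 36/0.75 = 48 at r = 0.5.

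At two-sided 0.05, the r at which 36 per arm reaches 80% power is, by the normal approximation, √(1 − 36/45.4), or about 0.45.

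**Step 3: the screening rule, as an illustration only.** The number of candidate covariates is not stated. If all were unrelated to outcome and independent, a p < 0.20 screen would admit at least one with probability 1 − 0.8⁵ = 67% for 5 candidates and 1 − 0.8¹⁰ = 89% for 10. On average it would admit 1 and 2 respectively.

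**The case against.** The strongest reply is that nothing here is an error. In a 1:1 randomised trial the unadjusted t-test is valid, its interval already allows for chance baseline imbalance, and it matches the test used to size the trial. That stands. A reader might infer that the primary estimate is biased, but the documents do not support that: the loss is precision only.

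The gain also rests on a correlation that the article does not give. At r = 0.2 the variance falls by only 4%, and power by about as little as the table shows. This limits any claim about size, but not the direction, since the cost is one degree of freedom.

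It could be said that covariate choice belongs in an analysis plan that is not shown. That would answer a complaint of silence. Here the article names the tests, and they are unadjusted.

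Other strong readings should be set aside:

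- **Power is 69%.** This holds only if alpha is two-sided 0.05 as worded. At one-sided 0.05, which reproduces 72, it is about 80%. That discrepancy is a separate matter.
- **The logistic models rest on screening alone.** They first name three variables, and intensity of pain may well mean baseline NRS, although the text does not say so.
- **Screening drives a primary test.** The responder outcome is assigned to chi-square. The logistic models are not described as the primary or non-inferiority analysis.
- **Baseline pain is ignored throughout.** The responder definition uses it, although the chi-square test does not adjust for it.
- **Nature of injury will not be collected.** The Baseline data list omits it, but that list is abbreviated: it also omits EQ-5D-5L, which Table 2 marks at baseline.

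**Conclusion.** The point holds as a matter of efficiency. The primary mean NRS comparison is fixed without adjustment, the obvious covariate is already collected, and adjusting would narrow the interval that decides non-inferiority.

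The size depends on the assumed correlation. For r from 0.2 to 0.5 the variance falls by 4% to 25%, which is worth roughly 2 to 12 percentage points of power at two-sided 0.05 and roughly 1 to 9 at one-sided 0.05. These figures take SD 1.7, 36 analysed per arm and no true difference. The low end is quite possible given the entry cut, so the change should not be counted on to bring 72 participants to 80% power under the two-sided reading.

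The screening rule is a secondary weakness, confined to supporting models of the responder outcome.

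**What to change.** Make the primary analysis of 3-month NRS a prespecified ANCOVA with arm and baseline NRS, or the 3-month contrast of a repeated-measures model with the same terms. Read the confidence interval of the adjusted difference against the 1-point margin. Keep the unadjusted t-test as a sensitivity analysis.

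For the logistic models of the 3-month responder outcome, delete the p < 0.20 screen and state a fixed covariate list that includes baseline NRS by name.

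Both changes are to analysis wording and should be settled before unblinding. The primary model costs one degree of freedom and needs no extra data or participants. Because r is unknown, treat the gain as a reserve and do not use it to reduce recruitment.
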